### Intervention: 7-day iCBT for social anxiety disorder group

The intervention program follows the THIS WAY UP iCBT program for social anxiety (available on www.thiswayup.org.au), using the intensive 1-week format introduced in the pilot trial [33] and described further in Table 1. Participants allocated to the intervention group (iCBT for SAD group) will be able to choose their preferred start date for the intervention as early as the week after the phone interview. To streamline tracking of participants and shared clinical care between research clinicians during business hours, participants are scheduled to begin their treatment on a Monday and end the following Sunday. A preparation call following a standardised script will be scheduled for the week prior to a participant’s treatment week, reiterating treatment week instructions, discussing their treatment goals, scheduling check-in calls for days 1 and 3, and answering any questions prior to commencement.

On the first day of the treatment week, participants will receive an automated email from the REDCap platform notifying them that their first module is available, with a written record of instructions for the coming week. Participants will complete baseline questionnaires prior to the first module. Each day participants are instructed to spend 20–30 min reading module content, before downloading a brief summary and activity plan, and spending 3–4 h over the remaining day practising the assigned skills.

Following treatment completion, participants will receive an automated email via REDCap with a link to complete post-treatment (T2) and follow-up (T3) questionnaires. At 6 weeks (T3), participants will complete the telephone diagnostic interview (SAD and MDD modules).

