### Control: waitlist control group

Participants allocated to the WLC group will be informed that they will be able to access the treatment after a waiting period of 6 weeks, during which they will complete three sets of online questionnaires. WLC participants will be sent automated emails via the REDCap platform with a link to complete questionnaires the day after their interview is completed (baseline, T1), 2 weeks later (T2), and 6 weeks post-baseline (T3). At T3, they will also be contacted to re-complete the telephone diagnostic interview, after which they will schedule the start date for their treatment week if they still choose to participate. WLC participants will follow the same procedure as the treatment group before (preparation call), and during their treatment week, receiving the treatment and clinician support over 1 week, and complete post-treatment questionnaires 1 week after completing their intervention. This post-treatment assessment will be used to assess WLC participants’ immediate treatment outcomes which will be included in the analysis of predictors of treatment outcome. The WLC will not be asked to complete any further follow-up assessments to minimise participant burden.

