### Randomisation and allocation procedures

At the completion of the telephone recruitment interview, participants will be randomised to either the iCBT for SAD group or WLC group using a 1:1 allocation ratio. Allocation numbers will be determined by a person who is completely independent of the research team, using the random.org random number generator and stored in opaque sealed envelopes, only opened by the study clinician once an offer of participation is made.

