### Trial outcomes and description of materials

After randomisation, all participants will complete a set of self-report questionnaires at baseline (T1), post-treatment (T2), and at 1-month follow-up (T3). Both groups will also be asked to complete a brief phone diagnostic interview [the ADIS MDD and SAD modules; [56]] at the 1-month follow-up (T3). Table 2 includes a list of assessment measures used and at which time point.

**Table 2 Tab2:** Materials used at each study time point

Questionnaire	Recruitment (T0)	Baseline (T1)	Post-treatment (T2)	One-month follow-up (T3)
Demographics	X			
Eligibility questions	X			
ADIS-5 modules	X			X
SPS	X	X	X	X
SIAS	X	X	X	X
PHQ-9	X	X	X	X
WSAS	X	X	X	X
LPFS-BF 2.0		X		X
PID-5-BF		X		X
HSU	X			
CEQ		X		
TSQ^a^			X	
Strategy use			X	X

^a^TSQ is completed by the treatment group only

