### Statistical analysis

All analyses will be undertaken using intention-to-treat approach. Linear mixed models, with a random intercept for subject will be used to analyse primary and secondary outcomes, and covariances matrixes used to assess relationships between variables. This approach will be used to manage missing data and account for correlation between repeated measures. Before conducting the analyses, patterns of missing data will be assessed through data visualisation, and Little’s Missing Completely at Random (MCAR) test to determine whether the data are missing at random. If there are significant group differences (as determined by independent samples *t*-tests) in the amount of time elapsed between the intake interview and completion of baseline measures, this variable will be included as a covariate in the linear mixed models. Planned contrasts will be used to compare pre- and post-treatment, and pre-treatment and 1-month follow-up, and planned pairwise comparisons will be used to compare between-groups at post-treatment and follow-up. To control for the risk of type 1 error with a co-primary outcome, the alpha level for significance will be adjusted using a Bonferroni correction (alpha set at 0.025 to determine statistical significance for the SIAS and SPS co-primary outcome measures). Linear mixed models will be utilised to test the predictors of treatment outcome. Within- and between-group effect sizes will be calculated using Hedges’ *g* (with 95% confidence intervals) to estimate the within-group changes from baseline to post-treatment, and baseline to follow-up, and between-group differences on primary and secondary outcome measures at post-treatment and follow-up.

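### The significance-triggered covariate for interview-to-baseline time adjusts the T2 and T3 group differences for a post-randomisation interval that the schedule itself makes unequal between arms

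*Protocol article*

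**What the plan says.** The Statistical analysis section sets a two-step rule. The trigger is a test: "If there are significant group differences (as determined by independent samples" t-tests). If it is significant, the "time elapsed between the intake interview and completion of baseline measures, this variable will be included as a covariate in the linear mixed models". The same section plans pairwise comparisons of the groups at post-treatment and follow-up, as well as contrasts from pre-treatment to each later time point. Trial design and setting names post-treatment (T2) as the primary time point.

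Four other statements determine what this interval is:

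- Randomisation and allocation procedures: "At the completion of the telephone recruitment interview, participants will be randomised".
- Trial outcomes and description of materials: "After randomisation, all participants will complete a set of self-report questionnaires at baseline (T1").
- Control section: waitlist participants are emailed a link to complete "questionnaires the day after their interview is completed (baseline, T1), 2 weeks later (T2), and 6 weeks post-baseline (T3").
- Intervention section: iCBT participants may "choose their preferred start date for the intervention as early as the week after the phone interview", and "participants are scheduled to begin their treatment on a Monday". They complete baseline before the first module.

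**The concern.** The interval begins when the participant is randomised and ends when baseline is completed, so all of it lies after randomisation. Its length depends on which schedule the participant was allocated to. A t-test on it asks whether two deliberately different schedules differ, and a significant result says nothing about chance imbalance.

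Once the covariate is in the model, it competes with arm for the same variation. The planned T2 and T3 group differences then depend on a slope that, when start weeks vary, is learnt mainly from iCBT participants who chose to start later. That slope is carried across a gap where few waitlist participants lie. Precision is lost in a trial with only 25 per arm. If people who delay are also more, or less, symptomatic, the slope picks up that selection and moves the estimated treatment effect.

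**Working it through.** **The plan's own figure.** For a standardised difference of 0.92, two-sided alpha 0.05 and power 0.80, the noncentral-t solution is 19.55, so 20 per group (power 0.81). This matches the Sample size calculations section. At the 0.025 level set for the co-primary outcomes, 25 per group gives power 0.82. That is the reference value below.

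**Inputs from the document.** There are 25 per arm; the waitlist link goes out on day 1; iCBT starts on a Monday, at the earliest in the week after the interview. An interview on Monday to Friday thus gives an earliest iCBT interval of 7, 6, 5, 4 or 3 days (mean 5, variance 2).

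**Assumed inputs, because the document gives none.** Interviews are spread evenly over weekdays. Waitlist completion takes 1 day plus a Poisson lag with mean m. iCBT participants all take the earliest Monday, or spread over several Mondays. The correlation between repeated scores is 0.6.

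**Formulae.** D is the difference in mean elapsed time, and v1 and v0 are the arm variances (v0 = m).

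- Expected trigger statistic: t = D / √((v1 + v0)/25).
- Variance inflation: VIF = 1 + D²/(4w), with w = (v1 + v0)/2.
- The covariate is constant over time, so it inflates only the between-person part of the T2 variance. SE multiplier = √[(ρ + (1−ρ)/3)·VIF + 2(1−ρ)/3], which at ρ = 0.6 is √(0.733·VIF + 0.267).
- Without the covariate, SE = √(2/25) = 0.283 SD.

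Worked example, earliest Monday with m = 1: D = 5 − 2 = 3; t = 3/√(3/25) = 8.7; VIF = 1 + 9/(4 × 1.5) = 2.5; SE multiplier = √(1.833 + 0.267) = 1.45.

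Power uses 25 divided by the squared multiplier as the effective number per arm, at alpha 0.025.

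| iCBT starts | Waitlist mean extra lag | D (days) | t | VIF | SE rise | Power (from 0.82) |
|---|---|---|---|---|---|---|
| Earliest Monday | 0.5 d | 3.5 | 11.1 | 3.45 | 67% | 0.33 |
| Earliest Monday | 1 d | 3.0 | 8.7 | 2.50 | 45% | 0.45 |
| Earliest Monday | 2 d | 2.0 | 5.0 | 1.50 | 17% | 0.67 |
| Earliest Monday | 3 d | 1.0 | 2.2 | 1.10 | 4% | 0.79 |
| 60/25/15% over 3 Mondays | 1 d | 6.85 | 6.3 | 1.79 | 26% | 0.59 |
| 60/25/15% over 3 Mondays | 3 d | 4.85 | 4.3 | 1.37 | 13% | 0.71 |
| 40/30/20/10% over 4 Mondays | 2 d | 9.0 | 6.2 | 1.76 | 25% | 0.60 |

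**Simulation check.** In simulated trials with mean lags of 1 to 3 days, the trigger fired in 99–100% of runs, except with earliest-Monday starts and a 3-day lag, where it fired in 59% at 25 per arm. Random-intercept models with three time points gave SEs of the T2 difference rising from 0.283 to between 0.344 and 0.461 at correlation 0.6 (22–63%). At correlation 0.7 they rose from 0.291 to 0.346 and from 0.275 to 0.396 (19–44%).

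**Bias.** If symptom level changes by b SD per day of delay within arm, adjustment shifts the T2 difference by about −b × D. With no link (b = 0) the shift is zero, and the simulated estimate stayed at about −0.92. For an assumed b of ±0.03:

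- Starts over three Mondays, D = 6.85: shift 0.03 × 6.85 = 0.21, so −0.92 becomes about −1.13 or −0.71 (simulated −1.13 and −0.69).
- Earliest Monday, D = 3: shift 0.09, so about −1.01 or −0.83 (simulated −1.01 and −0.83).

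**What is not affected.** The covariate moves the T1, T2 and T3 group differences by the same amount, so it cancels from the difference in change. In the simulations, with complete data, the group-by-time estimate and its spread were identical with and without it (for example −0.903, SD 0.214, both ways).

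**The case against.** The motive is sound. Because T2 is timed from T1, the unequal gap also makes the time from randomisation to T2 unequal, and the authors disclose a rule meant to address it. Four stronger readings are tempting, and the document does not support them.

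- **That allocation fixes the interval and the rule must fire.** The Control section fixes only when the waitlist link is sent; the rule concerns completion. Completing iCBT baseline on the Monday is a reasonable inference from the Intervention section, which says only that it precedes the first module. With slow waitlist completion and prompt iCBT starts, the trigger can miss, and the covariate then does little harm (VIF 1.1).
- **That the result is biased in favour of treatment.** Nothing in the document links delay to symptoms. The slope of 0.03 SD per day is illustrative, and the opposite sign is equally possible.
- **That the SE nearly doubles.** This needs every waitlist participant to complete on the day the link arrives (m = 0, VIF 5, multiplier 1.98). That is a limiting case for an emailed questionnaire.
- **That the whole efficacy analysis is damaged.** The group-by-time contrast escapes, and the plan also includes pre-to-post contrasts.

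What stands of the objection limits the size and certainty of the problem. It does not rescue the rule. When the rule fires reliably it costs precision in planned comparisons, including those at the primary time point, and when it does not fire it was not needed. Nor can it cleanly correct for elapsed time, since it cannot separate passage of time from who chose to wait.

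**Conclusion.** The point holds in a limited form. The rule conditions planned T2 and T3 between-group comparisons on a post-randomisation interval whose schedule differs by arm. Firing is near-certain under most plausible lags. The SE of those comparisons then rises by roughly 15–65%; at 25 per arm and alpha 0.025, power for 0.92 falls from 0.82 to between about 0.7 and 0.3 in the tabulated cases that fire reliably. Bias is conditional on a within-arm link between delay and symptoms, can go either way, and is absent without one. The group-by-time contrast is untouched with complete data. That the interval lies after randomisation and that the schedules differ follows from the article's text. The sizes rest on assumed completion lags, start-week spread and within-person correlation, which the investigators can replace with the recorded values.

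**What to change.** Remove the significance-triggered rule and fit the primary mixed model without elapsed time. Alternatively, rest the primary inference on the group-by-time contrast, or on a model adjusted for the T0 SIAS or SPS score, which Table 2 shows is collected at recruitment, before randomisation. Report elapsed time by arm, and enter it only in a sensitivity analysis labelled as such.

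Adjusting for T0 supplies a baseline that allocation cannot affect, but it does not equalise the time from randomisation to T2. That difference should be stated as a limitation.

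No new data are needed. The Trial status section says that data collection has finished and analysis is underway, so the change is a small deviation from the published plan. It should be dated and justified, and results under the published rule should be shown alongside as the sensitivity analysis.

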**Discussion:**

Previous findings from a pilot trial showed that 7-day iCBT is feasible and acceptable to clients with SAD. Based on these findings, we expect the treatment group will improve significantly on measures of symptoms of social anxiety, depression, and functional impairment compared to the WLC, and these improvements will be sustained at 1-month follow-up. If demonstrated to be effective in this RCT, intensive 7-day iCBT for SAD is a novel way to deliver CBT more quickly, with potential to reach more clients and reduce drop-out rates. It has great potential to provide rapid symptom improvement to individuals with SAD.

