Despite these encouraging initial findings, further investigation is needed to evaluate the program’s efficacy. Because of the lack of control group in the pilot trial, it is unknown whether the improvements observed were attributable to the treatment or to another factor, such as the passage of time or repeated assessments. Further, the study relied on self-report measures of social anxiety. The lack of follow-up assessment also means it is unknown whether the gains observed were maintained over the longer term. A RCT with a larger sample, comparison to a control group, and inclusion of follow-up and clinician-rated assessment is now needed to evaluate the efficacy of the program.

A further important area of investigation is for whom intensive iCBT is best suited. While an intensive online format has potential for rapid symptom improvement, unwanted side effects (e.g. feeling overwhelmed from time pressure) have been reported by some participants in intensive iCBT (e.g. [20, 21, 33]), so better understanding of which patients may benefit most from this new treatment format is important. One study [46] of standard-paced iCBT for SAD for example found that older age and female gender predicted better treatment adherence and outcome, while another [47] found lower baseline severity predicted better post-treatment outcomes. A meta-analysis of 28 studies of standard-paced CBT for SAD however found no consistent evidence for strong pre-treatment predictors of response across the studies [48]. It is also unclear whether the efficacy of intensive iCBT is impacted by common comorbidities in SAD, such as depressive symptoms and personality pathology, which have been shown to predict poorer treatment response in standard-paced CBT [48, 49]. We therefore sought to investigate these questions further by examining predictors of treatment response and adherence to intensive iCBT for SAD, including demographic characteristics (age, gender) and comorbid psychopathology (baseline severity of depression and SAD symptoms, personality pathology).

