## Methods

### Trial design and setting

This superiority trial will utilise a two-arm, parallel group RCT design with an equal allocation ratio. Outcome measures will be assessed at baseline, post-intervention (primary endpoint, measured at 2 weeks post-baseline), and follow-up (secondary endpoint, measured at 6 weeks post-baseline). The primary time point of interest is post-treatment (2 weeks post-baseline). A 6-week follow-up was selected to ensure participants in the control condition were provided with the intervention after a reasonable duration and to reduce participant attrition.

This clinical trial is sponsored by the University of New South Wales (UNSW) and ethics approval has been granted by the UNSW Human Research Ethics Committee (HREC; HC#220,089). The trial has been registered with the Australian New Zealand Clinical Trials Registry on March 1, 2022 (ACTRN12622000361707).

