## Discussion

The aim of our trial is to investigate the efficacy, acceptability, and feasibility of an intensive 1-week iCBT program for SAD compared to a waitlist control. To the best of our knowledge, this is the first RCT evaluating the efficacy of an intensive individually delivered 7-day iCBT treatment for any disorder including SAD. While our pilot trial [33] demonstrated preliminary evidence for the acceptability, feasibility, and positive outcomes of the intervention, including large reductions in social anxiety symptoms and functional impairment, the current study aims to extend these results using a more rigorous two-arm parallel-group RCT with follow-up.

The inclusion of a WLC group in this trial will allow for stronger conclusions to be made about treatment effects beyond external factors such as the passage of time, treatment expectancy, or clinician contact during the recruitment phase. The addition of clinician-rated measures and a diagnostic interview will enable us to assess the effects of the program on diagnoses of SAD and depression further to the self-report measures used in the pilot trial. Using validated clinical structured diagnostic interviews to assess SAD at baseline and follow-up will allow for stronger conclusions around intervention outcomes as they are less influenced by social desirability biases than self-report measures [93].

The study is strengthened by the inclusion of various outcome variables that explore the impact of the intervention beyond social anxiety symptoms, including on depression, quality of life, functional impairment, and personality traits and functioning. The inclusion of 1-month follow-up measures will also allow us to ascertain if treatment outcomes are sustained after the intensive 1-week treatment period.

The current study further extends the pilot trial as it is being completed outside of COVID-19 pandemic conditions. Significant increases in the use of online interventions for anxiety and depression were seen during the pandemic [94]. This study will allow us to ascertain whether the strong results and high levels of engagement found in the pilot trial are replicated in the current, post-pandemic period.

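### Follow-up is meant to show whether gains are sustained, but no planned comparison estimates change from post-treatment to follow-up, so relapse could be read as maintenance

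*Protocol article*

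**What the plan says.** Three places in the protocol article link follow-up to durability.

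- The Background, under 7-day iCBT for social anxiety disorder, criticises the pilot for having no follow-up: "it is unknown whether the gains observed were maintained over the longer term".
- The abstract's Discussion expects improvement "compared to the WLC, and these improvements will be sustained at 1-month follow-up".
- The main Discussion says the 1-month measures will "allow us to ascertain if treatment outcomes are sustained after the intensive 1-week treatment period".

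Statistical analysis lists the comparisons.

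- Within group: "Planned contrasts will be used to compare pre- and post-treatment, and pre-treatment and 1-month follow-up".
- Between groups: "planned pairwise comparisons will be used to compare between-groups at post-treatment and follow-up".
- Hedges' g with 95% confidence intervals for the same pairs. The within-group values are "to estimate the within-group changes from baseline to post-treatment, and baseline to follow-up"; the between-group values are at post-treatment and at follow-up.

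Trial design and setting makes T2 the primary time point and describes T3 as "follow-up (secondary endpoint, measured at 6 weeks post-baseline". The article does not define what would count as sustained.

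**The concern.** Maintenance concerns what happens between T2 and T3. Both within-group contrasts start from baseline, so a significant baseline-to-T3 change shows only that some gain remains, not that the T2 gain was kept. Two separate between-group tests do not fill the gap. Significance at both times does not show that the difference held, and significance at T2 alone does not show that it shrank.

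At stake is the support for one secondary claim. The listed analyses can show that participants are still better than baseline, or than waitlist, at 6 weeks. They give no interval for how much was lost after the treatment week.

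**Working it through.** **Inputs from the protocol article.** Pilot within-group gain on social anxiety, g = 1.26 to 1.9 (Background). Planning between-group effect 0.92, alpha 0.05, power 0.80, 20 per group needed and 25 recruited (Sample size calculations). Alpha 0.025 for each co-primary scale (Statistical analysis). Waitlist untreated until after T3 (Control: waitlist control group).

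**Assumptions.** The correlation r between visits is not given; r = 0.5, 0.7 and 0.8 are shown. Tests are two-sided. SDs are equal across visits, and the pilot g is treated as being in raw SD units. A paired t-test stands in for the mixed-model contrast.

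**1. The plan's own figure.** Two-sample noncentral t with d = 0.92 and alpha 0.05: 20 per group gives power 0.809, and 20/(1 − 0.20) = 25. The stated sample size reproduces.

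**2. Baseline-to-T3 contrast after losing half the gain.** The remaining g is 1.26/2 = 0.63. With dz = g/√(2(1 − r)), noncentrality dz × √20 and 19 df:

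| r | dz | noncentrality | P(significant), alpha 0.05 | alpha 0.025 |
|---|---|---|---|---|
| 0.5 | 0.63 | 2.82 | 0.76 | 0.65 |
| 0.7 | 0.81 | 3.64 | 0.93 | 0.87 |
| 0.8 | 1.00 | 4.45 | 0.99 | 0.97 |

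The smallest g significant at 0.025 is 2.433 × √(2(1 − r)/20) = 0.54, 0.42 and 0.34. So about 57%, 67% and 73% of a gain of 1.26 could disappear with the observed contrast still significant.

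**3. Randomised comparison at T3.** Two-sample noncentral t, noncentrality d × √(n/2):

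| Loss by T3 | d | n = 20, alpha 0.05 | n = 20, alpha 0.025 | n = 25, alpha 0.025 |
|---|---|---|---|---|
| none | 0.92 | 0.81 | 0.72 | 0.82 |
| a quarter | 0.69 | 0.57 | 0.45 | 0.55 |
| half | 0.46 | 0.29 | 0.20 | 0.26 |

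This test will often fail after a large loss. It also fails 28% of the time with no loss, and succeeds about 45% of the time with a quarter lost (n = 20, alpha 0.025). Neither result identifies whether the gain was kept.

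**4. Precision of the missing estimates, n = 20 per arm.**

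- T2-to-T3 change in the iCBT arm: half-width 2.093 × √(2(1 − r)/20) = 0.47, 0.36, 0.30 SD.
- Between-group difference in that change: half-width 2.024 × √(2 × 2(1 − r)/20) = 0.64, 0.50, 0.40 SD.

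The within-arm estimate is informative about a loss of 0.63 SD, although at r = 0.5 its power at alpha 0.025 is only 0.65. For a quarter of the gain lost (0.315 SD), that power is 0.18, 0.29 and 0.44. The between-group estimate is weaker: at r = 0.5 its half-width slightly exceeds 0.63 SD.

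**The case against.** A reader might infer that, under this plan, substantial relapse would be reported as sustained benefit. The article does not support that, for three reasons.

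- It states no rule that draws a conclusion of maintenance from the baseline-to-T3 contrast.
- It plans a between-group comparison at T3 that is still randomised, and the abstract words its expectation relative to the waitlist. Step 3 shows that this test would usually fail if half of the planning effect were lost.
- Effect sizes with intervals are planned at both times. In the example, 1.26 would stand beside 0.63 and attenuation would be visible.

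It can also be said that Trial aims and hypotheses frames follow-up as efficacy relative to waitlist, which the listed comparisons do test. Maintenance is not a formal hypothesis. T3 is secondary, and the short follow-up is acknowledged as a limitation. Nor does the article support calling early relapse the trial's main open question.

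All of this limits the point but does not remove it. The T3 test measures a difference at one time, not a change. Setting two effect sizes side by side gives the size of the attenuation but no interval for it, and their separate intervals ignore the correlation within participants. An unseen analysis plan might add the contrast, but the article enumerates its contrasts and repeats the same pairs for effect sizes, so the mismatch is with what it fixes.

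**Conclusion.** The point holds in limited form. The article says follow-up will establish whether gains are sustained, and no comparison or effect size it lists estimates T2-to-T3 change. Loss of about half the lower pilot gain could coexist with a significant baseline-to-T3 contrast, with probability 0.76 to 0.99 at alpha 0.05 or 0.65 to 0.97 at 0.025. The T3 between-group comparison is a partial safeguard, so the conclusion is that relapse could be misread, not that it would be.

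The figures rest on 20 analysed per arm, assumed r of 0.5 to 0.8, the paired-t approximation, and the pilot and planning effects taken at face value. The primary analysis at T2 and the sample size are unaffected.

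**What to change.** From the mixed model already specified, add for SIAS and SPS, each with a 95% confidence interval:

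1. the T2-to-T3 change in the iCBT arm;
2. as supportive evidence, the between-group difference in T2-to-T3 change.

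Base any statement that gains were sustained on these intervals. Do not read a non-significant change as maintenance, and report a wide interval as inconclusive. Trial status says data collection is complete and analysis under way, so label the contrasts as added after the published protocol if that is the case.

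If the contrasts are not added, limit the claim to participants still being better than baseline, or than waitlist, at 6 weeks.

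The cost is two extra contrasts on data already collected, with no new assessments and no change to the sample size. The downside is that both may be inconclusive, the second more often than the first.

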### Primary outcome measures

The co-primary outcome measures will be the Social Phobia Scale [SPS; [52]], a 20-item self-report measure of the respondent’s characteristic or typical fear of negative evaluation in social performance situations (e.g. public speaking, eating in front of others), and its companion measure, the Social Interaction Anxiety Scale [SIAS; [52]], a 20-item measure of anxiety related to social interactions (e.g. attending parties). These scales are frequently administered in tandem to comprehensively assess for both of these major components of social anxiety [58]. Both scales are widely used in clinical research, with studies demonstrating evidence of internal consistency (*α* = 0.89–0.94), test–retest reliability (*r* = 0.91–0.93) [52, 59], and construct validity, including concurrent validity, discriminant validity, and treatment sensitivity [52, 57–65].

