### Sample size calculations

The planned sample size is 50 participants, with participants randomly allocated to either a treatment group (*n* = 25) or a waitlist control group (*n* = 25). Power calculations are based on an estimated between-group effect size of 0.92 based on a meta-analysis of iCBT compared to controls [92] with alpha set at 0.05 and power at 0.8. A minimum sample of 20 participants per group is required to detect this effect size. An additional 5 participants per group will be recruited to account for expected attrition based on our pilot trial [33].

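### Fixed Bonferroni at 0.025 for SIAS and SPS is valid, but Holm's step-down gives the same 5% control and a better chance on the second scale

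*Protocol article*

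**What the plan says.** The Primary outcome measures section names two scales: "The co-primary outcome measures will be the Social Phobia Scale" and its companion, the SIAS. Trial design and setting gives one primary time point, post-treatment at 2 weeks post-baseline, so there are two primary between-group tests.

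For these, the Statistical analysis section states that "the alpha level for significance will be adjusted using a Bonferroni correction", with "alpha set at 0.025 to determine statistical significance for the SIAS and SPS co-primary outcome measures". The stated purpose is control of type 1 error. The article does not say whether the primary hypothesis needs one scale or both.

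The Sample size calculations section uses an effect size of 0.92 "with alpha set at 0.05 and power at 0.8". It concludes: "A minimum sample of 20 participants per group is required to detect this effect size". Five more per group are added for attrition, giving 25 per group. The Trial status section reports that data collection is finished and analysis is under way.

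**The concern.** Bonferroni keeps the second scale at 0.025 even after the first has been declared significant. Familywise control does not require this. Once one null hypothesis has been rejected at 0.025, only one remains on which a first false rejection could be made, and it can be tested at the full 0.05. The fixed split therefore gives up some power for no better protection against false positives.

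What is at stake is the claim on the second scale. The article uses the two scales together because they cover different components of social anxiety, interaction and performance. A true effect on both will more often be reported as an effect on one than the error rate requires. The trial is small, and its sample size was calculated at 0.05 rather than 0.025, so power on each scale is already limited.

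**Working it through.** **Inputs.** From the article: effect size 0.92, alpha 0.05 and power 0.80 for sizing, 20 per group minimum, 25 per group recruited, 1:1 allocation, 0.025 per scale in the analysis. Assumed, because the article does not give them: two-sided tests, the same effect of 0.92 on both scales, and the correlation between SIAS and SPS. The range of main interest is 0.5 to 0.8; 0 and 0.9 are shown as outer cases. Two-sample t-tests stand in for the planned mixed models.

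**1. The plan's own figures.** Bonferroni: 0.05 / 2 = 0.025, as stated. For the sample size, the noncentrality is d × √(n/2) = 0.92 × √10 = 2.909 on 38 degrees of freedom. At two-sided 0.05 the power is 0.81, and the smallest n reaching 0.80 is 20 per group, as stated. At 0.025 the same 20 per group give 0.72, and 24 per group are needed for 0.80. With all 25 per group retained, power at 0.025 is 0.82.

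**2. Why Holm keeps the 5% level.** Holm tests the smaller p-value at 0.025 and, only if that is significant, the other at 0.05.

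- Both nulls true: a false rejection needs at least one p ≤ 0.025, with probability at most 0.025 + 0.025 = 0.05 under any correlation.
- One null true: a false rejection needs that scale's p ≤ 0.05, with probability at most 0.05.
- Any p ≤ 0.025 is rejected under Holm too, so every Bonferroni rejection is kept.

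**3. Size of the gain.** Simulated correlated t-tests, 400,000 runs per setting, d = 0.92 on both scales. Arrows run from Bonferroni to Holm.

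| n per arm | Correlation | At least one scale | Both scales | Per scale |
|---|---|---|---|---|
| 20 | 0 | 0.92 → 0.92 | 0.51 → 0.65 | 0.72 → 0.78 |
| 20 | 0.5 | 0.86 → 0.86 | 0.58 → 0.69 | 0.72 → 0.77 |
| 20 | 0.7 | 0.83 → 0.83 | 0.61 → 0.71 | 0.72 → 0.77 |
| 20 | 0.8 | 0.81 → 0.81 | 0.63 → 0.72 | 0.72 → 0.76 |
| 20 | 0.9 | 0.78 → 0.78 | 0.65 → 0.74 | 0.72 → 0.76 |
| 25 | 0.7 | 0.91 → 0.91 | 0.74 → 0.82 | 0.82 → 0.86 |

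Consistency check: with equal effects, per-scale power is the mean of the at-least-one and both columns. At n = 20 and correlation 0.7, (0.825 + 0.608) / 2 = 0.717 for Bonferroni and (0.825 + 0.708) / 2 = 0.767 for Holm, as simulated.

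The at-least-one column cannot move, because Holm's first step is the same test at 0.025.

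**4. Smaller effect.** The Background section cites 0.79 against waitlist. At d = 0.79, n = 20 and correlation 0.7, both scales rise from 0.44 to 0.55 and per-scale power from 0.57 to 0.62.

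**5. Simulated error rates.** With both nulls true, the two rules have the same familywise error: 0.049, 0.043 and 0.037 at correlations 0, 0.7 and 0.9. With an effect on one scale only, Holm's false-positive rate on the other is 0.043, 0.040 and 0.038 at those correlations, against 0.025 for Bonferroni. All are below 0.05.

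**The case against.** The strongest reply is that nothing here is wrong. Bonferroni is prespecified, correctly calculated and slightly conservative; the article never calls it the most powerful rule, and the same remark could be made of any trial that uses it. This stands as far as error goes: no conclusion is put at risk. It does not make the choice neutral, because Holm has the same guarantee under the same assumptions and never rejects less.

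Four further limits also stand.

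- If support for the primary hypothesis needs only one significant scale, Holm does not change the chance of success. A reader might infer that the sponsor needs or wants an effect on both, but the article does not say so. If both were required, each could be tested at 0.05 with no adjustment, and Holm would not be the right remedy.
- A reader might take Holm as a cure for the low power. It is not one: the first rejection still needs p ≤ 0.025, while the sample size was derived at 0.05.
- The absolute power values depend on an assumed correlation, equal effects and t-tests. The planned repeated-measures mixed models may give different values.
- With analysis under way, replacing a prespecified primary rule by a more liberal one can look post hoc. The change is cheap in wording, but its timing matters.

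**Conclusion.** The point holds as an efficiency point. The fixed split at 0.025 is valid; Holm is uniformly at least as powerful at the same 5% familywise level. With 20 per arm, d = 0.92 on both scales and a correlation of 0.5 to 0.8, the gain is about 9 to 11 percentage points in the chance that both scales are significant and about 5 points in power per scale. With 25 per arm and correlation 0.7, the chance for both gains 8 points (0.74 to 0.82). The chance of at least one significant scale gains nothing.

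That Holm dominates Bonferroni needs no assumption about the correlation; the sizes of the gain do. The documents do not support reading this as a flaw that threatens the trial's conclusions, and the alpha mismatch between the sizing and the analysis is a separate matter that Holm leaves in place.

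**What to change.** Replace the fixed split by Holm: test the smaller of the two post-treatment p-values at 0.025 and, if it is significant, test the other at 0.05. In the same sentence, state whether the primary hypothesis is supported by one significant scale, and that the report will name which.

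Timing decides the status of the change. If the between-group primary results have not been seen, make it by a dated amendment. If they have been seen, keep Bonferroni as the primary rule and report Holm as a labelled supplementary analysis.

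The cost is a sentence or two in the analysis plan and no extra data. The one drawback is that confidence intervals matching Holm are less simple; 97.5% intervals for each scale can be shown instead.
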